### Trial entry questionnaires

At trial entry, women will be asked to complete a questionnaire relating to quality of life (as measured using the SF36 Health Survey Questionnaire) [36], satisfaction with care, anxiety (as measured by the Short Form Spielberger State Trait Inventory) [37], depression (as measured by the Edinburgh Postnatal Depression Scale) [38], physical activity [39] and other lifestyle factors that influence maternal weight gain in pregnancy, including a food frequency questionnaire [40].

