### Both study groups

All women in the trial will be asked to complete a questionnaire on health related quality of life [38] at 36 weeks gestation. They will also be asked about their physical activity [39] and dietary habits [40].

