• Maternal diet and exercise outcomes as measured by dietary and exercise [39] questionnaires at trial entry and 36 weeks gestation.

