### Analyses and reporting of results

An independent data monitoring committee will be established, with terms of reference. A multidisciplinary adverse events committee blinded to treatment allocation will review the cause of death for all maternal and infant deaths. These data will be made available to the independent Data Monitoring Committee. Recruitment will continue until sample size is reached followed by completion of data collection and analyses.

The analyses will follow several key steps. Baseline characteristics of all randomised women will be compared descriptively between the study groups. Outcome comparisons will be made according to the treatment allocation at randomisation on an ‘intention to treat’ basis. Both unadjusted and adjusted analyses will be carried out. Collaborating centre and OGCT result will be controlled for in all adjusted analyses. The primary outcome of large for gestational age and the secondary outcomes based on birth weight will be adjusted for maternal age, parity, body mass index, socioeconomic status and gestational age at entry.

Secondary exploratory analyses will consider baseline covariates that show evidence of imbalance between study groups and are related to the outcome of interest. The RRs and 95% CIs will be reported using log binomial regression for binary outcomes. The number needed to treat to benefit or harm for one adverse outcome will be calculated for the primary outcome. Continuous outcomes will be analysed using linear regression. All model assumptions, including normality, will be assessed. Statistical significance will be assessed at the 0.05 level using a two-sided comparative test.

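### The stated adjustment for 36-week diet and physical activity does not name the entry value of the same measure, which could enter only through an exploratory, imbalance-triggered analysis

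*Protocol article*

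**What the plan says.** The protocol article, under Secondary study outcomes, lists "Maternal diet and exercise outcomes as measured by dietary and exercise [39] questionnaires at trial entry and 36 weeks gestation". It does not say which of the two times is the outcome, or whether the outcome is the later value or the change.

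The same instruments are used twice. Trial entry questionnaires covers "physical activity [39] and other lifestyle factors that influence maternal weight gain in pregnancy, including a food frequency questionnaire [40". Both study groups says of 36 weeks: "They will also be asked about their physical activity [39] and dietary habits [40". The reference numbers for activity and for diet match.

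Analyses and reporting of results then sets the model and the covariates:

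- Model: "Continuous outcomes will be analysed using linear regression".
- Every adjusted analysis: "Collaborating centre and OGCT result will be controlled for in all adjusted analyses".
- The primary outcome and one class of secondary outcome get more: "secondary outcomes based on birth weight will be adjusted for maternal age, parity, body mass index, socioeconomic status and gestational age at entry".
- Everything else: "Secondary exploratory analyses will consider baseline covariates that show evidence of imbalance between study groups and are related to the outcome of interest".

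Both unadjusted and adjusted analyses are planned.

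**The concern.** When a score is measured before and after treatment, a woman's own earlier value is usually among the best predictors of her later one. Including it as a covariate narrows the confidence interval for the group difference without extra data. Here the article collects that value but leaves it out of the adjustment it names for diet and activity. The only stated way in is an exploratory analysis that depends on an observed imbalance. An entry score that is strongly prognostic but happens to be balanced would be left out.

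Dietary and lifestyle advice is the core of the intervention. If the primary result is null, the 36-week diet and activity outcomes are what would show whether behaviour changed at all. An interval wider than it need be makes that question harder to answer.

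**Working it through.** **Inputs from the article.** Total sample size is 682, with 4% loss to follow-up, 80% power and two-sided 5% significance (Sample size). No standard deviation, target difference or entry-to-36-week correlation is given for diet or activity.

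**The plan's own figure.** The only sample-size figure available is for the primary outcome, 14% against 7%. The usual two-proportion formula gives 300 per arm, or 600/0.96 = 625 after loss. With a continuity correction it gives 328 per arm, 656 in all, and 656/0.96 = 684 after loss, against 682 stated. The figure therefore reproduces with the correction. It has no bearing on this point beyond giving a number of women to work with.

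**Assumptions.** Allocation is 1:1, the score is continuous and analysed by linear regression, the variance is equal in the two arms, and r is the correlation between entry and 36 weeks. The 4% loss is applied to the questionnaires: 682 × 0.96 / 2 ≈ 327 per arm, 654 in all.

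**Formulas.** Let σ be the standard deviation of the 36-week score and n the number per arm.

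- Variance of the group difference without the entry score: 2σ²/n.
- With the entry score as covariate: 2σ²(1 − r²)/n. The proportion of variance saved is r².
- Reduction in interval width: 1 − √(1 − r²).
- Equivalent number of women: 654/(1 − r²).
- Difference detectable with 80% power, in units of σ: (1.96 + 0.84) × √(2/327) = 0.219 without the entry score, multiplied by √(1 − r²) with it.

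| Assumed r | Variance saved | Interval narrower by | Equivalent women | Detectable difference (SD) |
|---|---|---|---|---|
| not in model | – | – | 654 | 0.219 |
| 0.3 | 9% | 5% | 719 | 0.209 |
| 0.4 | 16% | 8% | 779 | 0.201 |
| 0.5 | 25% | 13% | 872 | 0.190 |
| 0.6 | 36% | 20% | 1,022 | 0.175 |
| 0.7 | 49% | 29% | 1,282 | 0.156 |

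**Why the imbalance trigger misses this.** The factor 1 − r² contains r but no imbalance term. Suppose the two arms have exactly equal mean entry scores. The estimates with and without the entry score then coincide, but the standard error without it is still σ√(2/n) rather than σ√(2(1 − r²)/n). The rule withholds the covariate in a case where it would still narrow the interval.

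**Why the form of the outcome should be fixed.** If the two named times were read as meaning a simple change score, with equal variance at both times, its variance relative to the 36-week value alone would be 2(1 − r). That is 1.4 at r = 0.3, 1.2 at 0.4, 1.0 at 0.5, 0.8 at 0.6 and 0.6 at 0.7. Below r = 0.5 a change score is less precise than ignoring the entry value. At every r in the table it is less precise than using the entry value as a covariate (0.91, 0.84, 0.75, 0.64, 0.51).

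**The case against.** The strongest reply is that this is a journal article. Covariates for one secondary questionnaire outcome are commonly left to a fuller protocol or analysis plan, and controlling for centre and OGCT sets a minimum that does not exclude others. This stands in part: nothing forbids adding the entry score, and an unseen plan may do so. But the article is not silent. It assigns covariates by class of outcome and states how any other baseline variable is to be considered. Under that rule the entry score is left to an exploratory, data-dependent route, and that choice can be judged as written.

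A reader might infer several stronger things that the documents do not support:

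- *That a quarter or more of the precision is lost.* A 25% saving in variance needs r of at least 0.5. A 25% narrower interval needs about 0.66, and a 25% gain in effective sample size about 0.45. No r is given, and at 0.3 to 0.4 the variance saving is only 9% to 16%.
- *That entry is treated as an outcome time.* The sentence may only say when the questionnaires are given. Baseline characteristics are to be compared descriptively, and no between-group test at entry is planned. The wording is unclear rather than wrong.
- *That chance baseline differences go uncorrected.* The exploratory route could pick up an imbalanced entry score.
- *That quality of life has the same problem.* It is not among the listed secondary outcomes. At entry it is tied to the SF36 [36], whereas the 36-week text cites [38], the reference given at entry for the depression scale. The same instrument is therefore not established.
- *That the entry questionnaire might follow disclosure of allocation.* Nothing in the article shows this.

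It is also fair to object that no completion rate is given for the 36-week questionnaires and that their scoring is not described. The equivalent numbers of women and detectable differences are therefore illustrative. The proportional savings do not depend on the number of women.

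**Conclusion.** The point holds as a matter of efficiency. Diet and physical activity are measured with the same questionnaires at entry and 36 weeks. The stated adjustment does not name the entry value, and the route left open for it depends on imbalance rather than on how well it predicts the outcome.

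The size rests on an assumed correlation: about 9% of the variance of the group difference at r = 0.3, rising to 49% at r = 0.7, for scores analysed by linear regression. The loss is of precision in a secondary outcome. There is no bias from the omission, and neither the primary outcome nor the sample size is affected. It is an improvement worth making because it is free, not a threat to the trial's validity.

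**What to change.** Under Secondary study outcomes, name 36 weeks as the outcome time for diet and physical activity, and describe the entry questionnaire as the baseline measurement.

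Under Analyses and reporting of results, state that the adjusted analysis of each diet or activity score will include the entry value of that same score, together with centre and OGCT result, whatever imbalance is observed. The imbalance-triggered exploratory rule would then no longer decide whether these entry scores are used. The planned unadjusted comparison can stay beside it.

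The cost is analysis wording only. The entry data are already planned for collection, and no extra women, visits or questionnaires are needed.

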### Sample size

The incidence of having a large for gestational age infant is the principal endpoint of the trial. In the Italian trial [32], 14% of infants born to women in the untreated group were large for gestational age compared with 6% in the infants of treated women, a 57% change. A trial of 682 women will be able to show a more conservative 50% reduction in risk of large for gestational age infants from 14% to 7% with dietary and lifestyle advice and treatment (5% level of significance, two – tailed alpha, 80% power, 4% loss to follow up).

This size of trial will be powered also to detect important differences in key secondary outcomes. The rate of serious health outcome for both the infant and the woman is 12.9% based on data from women with untreated borderline GDM in the Australasian Collaborative Trial of Supplements with vitamin C and vitamin E for the prevention of pre-eclampsia (ACTS) [7]. The sample size of 682 women will allow a 51% reduction in the risk of serious maternal and infant health outcome from 12.9% to 6.3% to be detected with 80% power.

### Analyses and reporting of results

An independent data monitoring committee will be established, with terms of reference. A multidisciplinary adverse events committee blinded to treatment allocation will review the cause of death for all maternal and infant deaths. These data will be made available to the independent Data Monitoring Committee. Recruitment will continue until sample size is reached followed by completion of data collection and analyses.

The analyses will follow several key steps. Baseline characteristics of all randomised women will be compared descriptively between the study groups. Outcome comparisons will be made according to the treatment allocation at randomisation on an ‘intention to treat’ basis. Both unadjusted and adjusted analyses will be carried out. Collaborating centre and OGCT result will be controlled for in all adjusted analyses. The primary outcome of large for gestational age and the secondary outcomes based on birth weight will be adjusted for maternal age, parity, body mass index, socioeconomic status and gestational age at entry.

Secondary exploratory analyses will consider baseline covariates that show evidence of imbalance between study groups and are related to the outcome of interest. The RRs and 95% CIs will be reported using log binomial regression for binary outcomes. The number needed to treat to benefit or harm for one adverse outcome will be calculated for the primary outcome. Continuous outcomes will be analysed using linear regression. All model assumptions, including normality, will be assessed. Statistical significance will be assessed at the 0.05 level using a two-sided comparative test.

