### Primary study outcomes

The primary study outcome will be incidence of large for gestational age infants defined as birthweight above the 90^th^ centile for gestation and fetal sex on standardised birthweight charts [43].

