• Other causes of infant morbidity as defined by: individual components of the composite infant outcome; neonatal jaundice requiring phototherapy; neonatal hypoglycaemia requiring treatment (defined as blood glucose <2.5 mmol/L); shoulder dystocia; nerve palsy; bone fracture; gestational age at birth; preterm birth (less than 37 weeks gestation); Apgar score <7 at five minutes; weight, length, head circumference, small for gestational age (<10^th^ percentile for gestation and fetal sex on standardised birthweight charts [43]); macrosomia (≥4 kg); need for admission to the neonatal nursery and length of stay; and need for admission to neonatal intensive care and length of stay; incidence and severity of respiratory distress syndrome, use of and length of mechanical ventilation, intraventricular haemorrhage on early cranial ultrasound, periventricular leukomalacia on later cranial ultrasound, need for oxygen therapy at 28 days or more of life, use of postnatal steroids, use of antibiotics in first 48 hours of life, proven systemic infection in first 48 hours of life, use of antibiotics after first 48 hours of life, proven systemic infection after first 48 hours of life; use of surfactant; nitric oxide for respiratory support; need for inotropic support; air leak syndrome; retinopathy of prematurity; patent ductus arteriosus requiring treatment; number of episodes of proven infection; proven necrotising enterocolitis; thrombocytopenia; neonatal encephalopathy (Sarnat Stage 1, 2 or 3) [46].

For the mother, the secondary outcomes will be

• serious health outcomes up to six weeks postpartum as defined by one or more of maternal death; pulmonary oedema; eclampsia; stroke; adult respiratory distress syndrome; cardiac arrest; respiratory arrest; placental abruption; haemolysis; coagulopathy; major postpartum haemorrhage; deep vein thrombosis or pulmonary embolism requiring anticoagulant therapy.

• other adverse health outcomes as defined by: individual components of the composite maternal outcome; pre-eclampsia [47]; caesarean birth; induction of labour; need for antenatal hospitalization and length of stay; antepartum haemorrhage requiring hospital admission; weight gain during pregnancy; use of antihypertensive medication; chorioamnionitis requiring antibiotics during labour; length of postnatal hospital stay; use of postnatal antibiotics; and postpartum haemorrhage (≥500mls).

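### The adjusted linear models for birthweight, length and head circumference omit infant sex, and those for length and head circumference also omit the five maternal covariates, which gives up a little precision

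*Protocol article*

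**What the plan says.** The section Analyses and reporting of results plans unadjusted and adjusted analyses and gives a covariate rule in two tiers.

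- Tier one, for every outcome: "Collaborating centre and OGCT result will be controlled for in all adjusted analyses".
- Tier two, for the primary outcome and a subset of secondary outcomes: "the secondary outcomes based on birth weight will be adjusted for maternal age, parity, body mass index, socioeconomic status and gestational age at entry".

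Infant sex appears in neither tier. The same section says "Continuous outcomes will be analysed using linear regression".

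The section Secondary study outcomes lists "weight, length, head circumference, small for gestational age" among the infant outcomes. Of these four, only small for gestational age is standardised by chart; the other three are raw measurements. Birthweight falls naturally under tier two. Length and head circumference do not.

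Sex enters the plan through outcome definitions. The primary outcome is "birthweight above the 90^th^ centile for gestation and fetal sex on standardised birthweight charts", and small for gestational age and severe growth restriction are defined on the same charts.

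One other route is offered for further covariates: "Secondary exploratory analyses will consider baseline covariates that show evidence of imbalance between study groups and are related to the outcome of interest".

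**The concern.** By using sex-specific charts, the protocol treats sex as a determinant of birthweight. When weight is then analysed in grams, nothing accounts for sex, and the same is true of length and head circumference. Length and head circumference also miss the five maternal covariates that the plan considers worth adjusting for in birthweight, although all three measure fetal growth.

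These are suitable covariates. Infant sex is settled before randomisation, cannot be changed by treatment, and must be recorded to derive the primary outcome. The maternal covariates must be available for the adjusted primary analysis. Adjusting a linear model for such predictors removes outcome variance and leaves the target of estimation unchanged.

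What is at stake is the width of three confidence intervals: how easily a real shift in weight, length or head circumference would be seen.

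**Working it through.** **1. The plan's own figure.** The Sample size section assumes a "50% reduction in risk of large for gestational age infants from 14% to 7% with dietary and lifestyle advice and treatment", two-sided 5% significance, 80% power and 4% loss, and gives 682 women.

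- Uncorrected n per group = [1.96 × √(2 × 0.105 × 0.895) + 0.842 × √(0.14 × 0.86 + 0.07 × 0.93)]² / 0.07² = 300.
- With the continuity correction: 328 per group, 656 in total; 656 / 0.96 = 684 after rounding up. This agrees with 682 to within rounding.
- Without the correction: 600 / 0.96 = 625, which does not.

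The figure rests on a binary, sex-standardised outcome, so the present point does not affect it.

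**2. Infants analysed.** 682 × 0.96 / 2 = 327 per group, taking equal allocation from the balanced blocks. With no covariates, the standard error of a mean difference is √(2/327) = 0.078 SD and the 95% half-width is 1.96 × 0.078 = 0.153 SD.

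**3. Variance explained by sex.** With half the infants boys, a sex difference D and a standard deviation SD, R² = (D/2)² / SD². The standard error is multiplied by √(1 − R²). The documents give neither D nor SD, so the values below are assumptions. Each row pairs the smaller D with the larger SD, then the larger D with the smaller SD.

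| Outcome | Assumed D | Assumed SD | R² | Fall in standard error |
|---|---|---|---|---|
| Birthweight | 100 to 150 g | 550 to 450 g | 0.8% to 2.8% | 0.4% to 1.4% |
| Length | 0.5 to 1.0 cm | 2.5 to 2.2 cm | 1.0% to 5.2% | 0.5% to 2.6% |
| Head circumference | 0.4 to 0.8 cm | 1.6 to 1.4 cm | 1.6% to 8.2% | 0.8% to 4.2% |

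**4. Sex plus the five maternal covariates, for length and head circumference.** Assume a combined extra R² of 5% to 10%; the documents give no figure for this either.

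- Standard error: √0.95 = 0.975 and √0.90 = 0.949, a fall of 2.5% to 5.1%.
- Half-width: 0.153 SD becomes 0.149 to 0.145 SD.
- Power, for a difference that has 80% without these covariates: Φ(2.80/0.975 − 1.96) = 82% and Φ(2.80/0.949 − 1.96) = 84%.
- Equivalent sample: 654/0.95 = 688 and 654/0.90 = 727, that is 34 and 73 more infants.

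**5. Cost.** Six extra parameters, if each covariate takes one, cost about 6/655 = 0.9% of variance. Sex alone costs 1/655 = 0.15%. Net of cost, the variance ratios in step 4 become 0.95 × 1.009 = 0.959 and 0.90 × 1.009 = 0.908, so the standard error falls by about 2.1% to 4.7%. The six covariates gain nothing if together they explain less than about 0.9%.

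**6. Chance imbalance in sex.** The standard deviation of the difference in the share of boys is √(2 × 0.25/327) = 0.039. One trial in 20 therefore differs by at least 1.96 × 0.039 = 7.7 percentage points. With d = D/SD, such a difference shifts the comparison by 1.96 × √(0.5/n) × d. Divided by the standard error √(2/n), this is 1.96 × d/2 standard errors. Dividing by 1.96 and squaring gives (d/2)², which is the R² of step 3. For head circumference at the top of the range, d = 0.57 gives a shift of 0.56 standard errors and returns R² = 8.2%. Imbalance is thus the same variance seen from another side.

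**The case against.** The strongest reply is that nothing here is wrong. The plan prespecifies unadjusted and adjusted analyses, puts the stratification factors in every adjusted model, and gives the primary outcome a richer set. All these estimates are unbiased under randomisation, so a longer covariate list for three items in a very long list of secondary outcomes may be no more than preference. It stands that this is neither an error nor a contradiction.

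A second reply is that tier one sets a minimum, and that a journal article leaves covariates outcome by outcome to the full protocol or analysis plan. This has some force: those documents may well extend the list. But the article does not stay silent. It names the covariates and the outcomes they serve, and that published rule is the one at issue.

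A third reply is the exploratory route for imbalanced covariates. It is a weak substitute. It depends on the observed data, is labelled exploratory, and is limited to baseline covariates; whether infant sex, normally recorded at birth, counts as one is arguable. It also misses the gain available when the groups are balanced.

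Finally, the size rests on assumed values, and this stands in full. The combined R² for the maternal covariates has no support in the documents.

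A reader might infer more than the documents support:

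- That the growth results would be biased, or that a chance excess of boys is a further harm. Randomisation excludes the first. Step 6 shows the second is already counted, and the unadjusted interval already allows for it.
- That the trial's main growth conclusion is weakened. That conclusion rests on large for gestational age, which the charts already standardise for sex.
- That the precision is entirely free. It costs about 1% of variance.

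**Conclusion.** The point holds as a small efficiency suggestion. As the article is written, the adjusted models for the three raw size measures leave out infant sex, and two of them also leave out the maternal covariates used elsewhere. For birthweight the loss is slight, at most about 1.4% of the standard error under the assumed values. For length and head circumference it is about 2.5-5% before the parameter cost, if sex and the maternal covariates together explain 5-10% of variance. At the low end of the assumptions the gain could be close to nil. The change is worth making because it needs no new data and, if fixed beforehand, avoids a later choice driven by the data. It ranks as nice to have, with medium confidence.

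**What to change.** Before analysis, amend the covariate sentence in Analyses and reporting of results in two ways:

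1. Add infant sex to the adjusted linear models for birthweight, length and head circumference.
2. Apply to length and head circumference the same five maternal covariates as to the birthweight outcomes.

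Leave large and small for gestational age unchanged, since the charts already standardise them for sex. Do not add gestational age at birth: it arises after randomisation and treatment may affect it.

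The cost is one sentence of analysis wording, with no extra data collection and no extra women. If the full protocol or analysis plan already specifies these models, it is enough to confirm that it does so.
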